## Abstract

**Objective:**

Epilepsy is a common condition associated with significant morbidity, mortality, and costs. Poor documentation of seizures is a major challenge in epilepsy care. Objective seizure counting with mobile devices may mitigate this challenge and improve patient management. The aim of this study is to investigate whether ultra long‐term subcutaneous EEG improves seizure documentation and disease monitoring in people with drug‐resistant epilepsy.

**Methods:**

Real World Testing and Cost‐effectiveness Analysis of Subcutaneous EEG (REAL‐ASE) is a UK‐based multi‐centre prospective interventional study with an expected duration of 7 months. Thirty‐three adult participants will be implanted with 24/7 EEG SubQ and collect 2‐channel EEG data for 6 months. Data will be reviewed and annotated by experts, and a summary sent to the treating clinician weekly. The treating clinician will communicate information from this annotation report to participants monthly. Changes in management can be made at the treating clinician's discretion. REAL‐ASE was approved by the Bromley Research Ethics Committee in July 2023 (reference number 23/LO/0419).

**Results:**

We anticipate that subcutaneous EEG may improve seizure documentation and be a well‐accepted addition to epilepsy care by clinicians and patients. We believe it will be associated with better quality of life and will be a cost‐effective solution.

**Significance:**

If our study demonstrates improved seizure documentation with subcutaneous EEG, this may contribute to patient safety, improved quality of life, and a reduction in healthcare costs.

**Plain Language Summary:**

We present a clinical trial protocol for a prospective cohort study of 33 people with epilepsy across the UK. The study aims to assess whether an EEG implant placed under the skin: (1) is more accurate than patient‐reported seizure diary, (2) is feasible and acceptable to patients and clinicians, (3) reduces the impact of epilepsy, and (4) is beneficial to the National Health Service (NHS).

Key points
Current guidelines emphasize regular seizure frequency assessments. Patient diaries are ubiquitous, but evidence shows they are unreliable.There have been no previous clinical trials to evaluate the role of a CE‐marked subcutaneous EEG device within the NHS.We describe a clinical trial protocol assessing the utility of two‐channel subcutaneous EEG compared to patient‐reported seizure diaries.This trial will evaluate whether the use of subcutaneous EEG can improve seizure frequency documentation in the outpatient setting.

## INTRODUCTION

1

### Background and rationale

1.1

Epilepsy is a common disorder. In the UK, approximately 550 000–800 000 people are currently being treated for epilepsy in the National Health Service (NHS).^1^, ^2^ Epilepsy is also costly, with the total direct cost in the European Union estimated at €15.5billion,^3^ particularly related to the costs of anti‐seizure medications and the costs of emergency admissions.^4^ Epileptic seizures are one of the commonest reasons for repeated emergency admissions in the NHS.^5^ Seizures are the key symptom of epilepsy and the most important predictor of quality of life.^6^ Approximately 30% of people with epilepsy have seizures despite being on apparently optimal treatment.^7^ Tragically, epilepsy is the 5th leading cause of avoidable years of life lost in males, and the 8th leading cause in females,^8^ with most of these deaths directly attributable to the consequences of seizures.

The majority (60%–68%) of people with epilepsy experience focal seizures.^9^, ^10^, ^11^, ^12^ A recent meta‐analysis revealed focal‐onset seizures conferred a relative risk of 3.36 for treatment resistance.^13^

In clinical practice, a participant‐reported seizure diary is the ubiquitous outcome measure to evaluate the effectiveness of anti‐seizure medications.^14^ There is strong evidence that participant‐reported seizure diaries are unreliable. For example, using in‐hospital video‐EEG as the ground truth for seizure documentation, studies found 44%–56% of seizures were not reported.^15^, ^16^, ^17^ Reasons for under‐reporting seizures might include unawareness that a seizure has occurred, post‐ictal amnesia, seizures occurring during sleep, uncertainty about the number of seizures occurring during a cluster, and incomplete adherence to keeping a diary. In a study using a device recording intracranial EEG in 11 participants for several months, the average correlation between monthly diary seizure counts and monthly ground truth intracranial EEG‐detected seizure counts was weak, only 0.30.^18^ Poor seizure documentation may lead to suboptimal management. Patients who fail to report seizures are at increased risk of seizure‐related harm, and patients who over‐report certain symptoms as seizures may be at risk of excessive treatment side effects.

The need for more objective seizure monitoring has led to the development of several mobile health technologies.^19^, ^20^ To date, most are approved for the detection of generalized or focal‐to‐bilateral tonic–clonic seizures. Furthermore, there is very limited real‐world evidence to support the reliability of most devices, as most evidence is generated from recordings in the hospital environment or in supervised care settings. Hence, there is a critical gap for a portable, discreet device able to detect a wider range of seizure types, particularly focal seizures.

There has been rapid development of EEG‐based mobile technologies, such as subcutaneous EEG. To date, one device has received CE mark for ultra long‐term ambulatory EEG recording—the 24/7 EEG SubQ system (UNEEG Medical; Allerød, Denmark) illustrated in Figure 1.^21^

**FIGURE 1 epi470064-fig-0001:**
[figure not shown]
Main components of the 24/7 EEG SubQ solution (UNEEG medical). (A) The implant consists of a lead with three electrodes and a ceramic housing with the electronics. (B) The external device powers the implant and enables recording of the data. (C) The implant is implanted entirely subcutaneously. (D) The device attaches to the clothes via a plastic clip (C1) or a disc‐shaped magnet. (E) For recording, the wire and disc of the external device attach to the skin overlying the implant housing with a small adhesive patch. Once a day, the external device is attached to a tablet for charging and transferring the data via a cloud‐based solution to the healthcare professional (HCP).

Using the 24/7 EEG SubQ system, it is feasible to record EEG data reliably from home for up to 15 months.^22^, ^23^ Preliminary data suggest the device has recording characteristics similar to scalp EEG (for 2 bipolar channels),^24^ with signal quality showing high long‐term stability.^22^ Observational studies have suggested its utility for objective seizure counting, including the detection of temporal periodicities of seizure occurrence.^25^, ^26^ However, it remains uncertain whether this tool is of demonstrated added value when used prospectively, in the real world.

### Objectives

1.2

The primary objectives for this study are to investigate whether 24/7 EEG SubQ, (1) is more informative than a participant‐reported seizure diary, (2) is feasible and acceptable to participants and clinicians, (3) reduces the impacts of epilepsy and improves quality of life, and (4) provides gains to the healthcare system when rolled out into the NHS.

## METHODS

2

### Trial design

2.1

REAL‐ASE (Clinical Trials NCT06144047) is a prospective, non‐randomized, multicentre, interventional study that will be performed across UK neurology centres. A total of 33 adults with epilepsy, treated as part of their routine clinical care across the recruitment sites, will be enrolled.

### Study setting

2.2

The study will take place in UK hospitals with integrated neurology centres, recruiting participants as outpatients.

### Eligibility criteria

2.3

Inclusion criteria are: (1) given written informed consent; (2) adults (≥18 years of age); (3) routinely keep a seizure diary, have access to a smartphone, and are willing to use the electronic diary for the study; (4) experiencing 10 or more seizures per year according to the seizure diary; (5) have had an epilepsy diagnosis for at least 2 years; and (6) willing to comply with study procedures.

Exclusion criteria are: (1) cochlear implant(s); (2) established current diagnosis of psychogenic non‐epileptic attacks (dissociative seizures); (3) frequent vigorous involuntary movements (e.g. chorea, athetosis) or frequent parasomnias with major motor components (e.g. sleep walking, night terrors); (4) participants involved in therapies with medical devices that deliver electrical/radiofrequency energy into the area around the implant; (5) participants at high risk of surgical complications, such as active systemic infection and haemorrhagic disease; (6) allergy to the local anesthetics used during implantation; (7) infection at the site of device implantation; (8) participants who operate MRI scanners or are planned to have an MRI scan during the study period; (9) participants with profession/hobby that includes activity imposing extreme pressure variations (e.g. diving or parachute jumping). NB: diving/snorkeling is allowed to 5 meters of depth; (10) participants with profession/hobby that includes activity imposing an unacceptable risk for trauma against the device or the site of implantation (e.g. martial art or boxing); and (11) Any other serious medical condition that in the opinion of the Chief Investigator would be incompatible with participation in the study.

### Sample size

2.4

We powered our study based on the primary outcome measure for diagnostic accuracy. We used data from an intracranial EEG study,^18^ which shows the correlation between the monthly number of seizure occurrences documented using participant self‐reported diary and the ground truth seizure occurrences per month, documented with the intracranial Neurovista device. The mean correlation across the group is 0.30 (SD 0.41). We seek to demonstrate a higher correlation between 24/7 EEG SubQ and the ground truth seizure occurrences. We chose a modestly higher correlation of 0.5 to power this study. At alpha 0.05, 33 participants would give 85% power to demonstrate an improvement in within‐participants correlation from 0.3 to 0.5 (calculated using G*Power).

### Recruitment

2.5

People with epilepsy (PWE) will be identified by investigators through epilepsy clinic attendance lists, electronic patient records, and hospital Epilepsy Monitoring Unit admission lists at the participating sites. Potential participants will be approached by telephone, email, letter or in clinic by an investigator. This contact will be designated the ‘first approach’ and will involve providing the participant information leaflet. Subsequently, after at least 24 hours, potential participants will be invited to a face‐to‐face meeting (Visit 1) during which they will be given the opportunity to discuss the study. If they opt to enroll in the study, they will provide informed consent to participate.

## STUDY PROCEDURES

3

During Visit 1, participants will complete baseline patient reported outcome measures (PROMs) and subsequently will undergo an online qualitative interview at baseline. Following this, they will be implanted with the 24/7 EEG SubQ by the local surgical team (Visit 2). The implant is inserted under local anesthesia in the pre‐auricular region in the subgaleal space on a predetermined side (i.e. right or left) and orientation based on the treating clinician's instruction. The electrodes can be positioned anywhere in the arc illustrated on the right of Figure 1 panel C, which allows a wide range of focal epilepsies to be included. We aim to position the electrodes where ictal EEG changes are likely to be detected based on previous electroclinical data. Any surgical specialty with expertise operating within the head and neck region is eligible to implant the 24/7 EEG SubQ. The participant is discharged after a two‐hour observation period with an implant ID card. Visit 3 occurs 10–14 days after implantation, when procedures for data collection will again be explained, and the participant will commence EEG data collection and begin keeping an electronic seizure diary (Helpilepsy; Neuroventis, Overijse, Belgium).^27^ During 6 months of data collection, participants will receive a minimum of monthly feedback regarding recorded EEG data from their treating clinician. They will repeat PROMs at 2 months (Visit 4) and 6 months (Visit 5) and an online qualitative interview prior to explantation after data collection is complete. The participant will then exit the study. Treating clinicians will complete standardized questionnaires assessing their experience using the 24/7 EEG SubQ during the study and after the participant's last visit. A treating clinician at each site will participate in a qualitative interview after the last participant at that site has had his/her final visit.

The study investigators will provide careful and detailed explanation about study procedures (including follow up plans) during the first approach, follow up approach, and Visit 1. Participants will be reminded of study visits prior to their occurrence. Participants will be provided with study point of contact details (Study Co‐ordinator and Clinical Research Fellow) and will be given ample notice for visit dates and times. There will be an option to complete Visits 4 and 5 remotely by phone if this is more convenient. Clinician monthly feedback to participants can be given through any preferred medium, as agreed between participant and clinician. See Figure 2 for complete study schedule.

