### Data collection

3.1

PROMs will be collected at Visits 1 (baseline), 4 (2 months), and 5 (6 months) via the electronic data capture system REDCap (see Table 1 for details).^28^ Use of REDCap forced responses to progress surveys and email prompts to review data will be utilized to ensure data completeness with both participants and investigators.

**TABLE 1 epi470064-tbl-0001:** Primary and secondary objectives with corresponding outcome measures.

Primary objective	Corresponding endpoint(s)/outcome variable(s)
To investigate the diagnostic accuracy of 24/7 EEG™ SubQ Solution	Within‐participant correlation between seizure counts per month estimated from rapid clinician review of annotated 24/7 EEG™ SubQ data and ‘ground truth’ EEG seizure occurrences per month (derived from expert research team review of 24/7 EEG™ SubQ EEG data), across the 6 months of the study (‘correlation A’). Within‐participant correlation between seizure counts per month from participant‐reported seizure diary and ‘ground truth’ EEG seizure occurrences per month (derived from expert research team review of 24/7 EEG™ SubQ EEG data), across the 6 months of the study (‘correlation B’). Average difference between ‘correlation A’ and ‘correlation B’, across participants. Average difference between the number of AI‐driven automated seizure detections produced by EpiSight software and seizure counts estimated from rapid clinician review of annotated 24/7 EEG™ SubQ data, across participants. Clinician rating on the question ‘Overall, after review of annotated 24/7 EEG™ SubQ data for all participants, how would you rate your rapid clinician review?’, i.e., average score on a 10‐point Likert scale (‘the AI‐driven algorithm is very accurate compared to my rapid review’ (10) to ‘the AI‐driven algorithm is very inaccurate compared to my rapid review’ (1))

Secondary objectives	Corresponding endpoint(s)/outcome variable(s)
2 To investigate the clinical relevance of 24/7 EEG™ SubQ Solution	Change over time for average HCP questionnaires ‘Communication’, ‘Insight’ & ‘Potential of 24/7 EEG™’ scores at baseline, 2 months and 6 months

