3 To investigate if the EEG data recorded with 24/7 EEG™ SubQ might be used to inform change(s) in clinical management plan for the participant	Proportion of investigators (i.e., treating clinicians) with a positive opinion, i.e., answer ‘Yes’ to the question ‘Did you adjust or change the clinical management plan during the past month?’ ‘(Yes/No)’. B Investigators rating of which data provided by 24/7 EEG™ SubQ Solution and/or clinical data led to change(s) of the clinical management plan: (i) Electrographic seizure, (ii) seizure type, (iii) seizure frequency, (iv) seizure severity, (v) cluster patterns, (vi) seizure periodicity, (vii) trigger factors, (viii) side effects of current anti‐seizure medication, (ix) lack of effects of current anti‐seizure medication, (x) non‐adherence to anti‐seizure medication, (xi) indication for adjusting or changing anti‐seizure medication, (xii) other. C Investigators rating of which adjustment(s) or change(s) to the epilepsy management plan initiated based solely or partly on data provided by 24/7 EEG™ SubQ Solution during the past month: (i) advice/education, (ii) referral, (iii) adjusting or changing anti‐seizure medication, (iv) prescription of other than anti‐seizure medication, (v) increased clinical follow‐up, (vi) changes in primary care, (vi) further examinations/test, (vii) other. D Investigators reason(s) for not changing the clinical management plan, i.e., answering ‘no’ on 3.A: (i) The patient is optimally treated (ii) Patient resistance to change in management plan despite medical, (iv) Insufficient data or information to adjust or change the clinical management plan) (v) other (free text). E Change over time for average HCP questionnaire ‘Management’ scores at baseline, 2 months and 6 months
4 To investigate participants' perception of the value of receiving feedback about seizure occurrences estimated from EEG data recorded with 24/7 EEG™ SubQ	Participants overall rating of the value of receiving feedback about seizures occurrences every month, across the full study period, from the EEG data recorded with 24/7 EEG™ SubQ i.e., average score on a 10‐point Likert scale (‘I found the feedback about when seizures had occurred according to the 24/7 EEG™ SubQ extremely helpful’) (10) to negative (‘I found the feedback about when seizures had occurred according to the 24/7 EEG™ SubQ extremely unhelpful’) (0))

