### Statistical analysis of primary outcome measures

4.1

The research team will review raw EEG data from 24/7 EEG SubQ to identify seizures as the ‘ground truth’. We will assess the improvement in accuracy of seizure documentation using AI‐driven algorithm with rapid expert review applied to 24/7 EEG SubQ data (‘24/7 EEG SubQ detected seizures’), compared to using self‐reported participant diary alone. We will estimate for each participant the Spearman correlation between monthly diary report and ground‐truth, and the Spearman correlation between monthly 24/7 EEG SubQ detected seizures and ground truth. We will test the hypothesis that, across the cohort, the correlation between 24/7 EEG SubQ detected seizures and ground truth is higher than between the diary and ground truth. We will also calculate for diary and 24/7 EEG SubQ detected seizures the sensitivity, specificity, false positive rate, positive predictive value, and negative predictive value, for seizure detection. We will report using Standards for the Reporting of Diagnostic accuracy studies (STARD) principles.^31^

Feasibility and acceptability will be assessed by the proportion of participants who continue in the study for >3 months of 24/7 EEG SubQ data collection.

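### Correlation B comes from a diary kept under at least monthly EEG feedback, so it is open to contamination and is not the diary-alone comparator that section 4.1 names

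*Protocol article*

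**What the plan says.** - **Timing.** Section 3 (Study procedures) starts recording and diary together: at Visit 3, 10–14 days after implantation, "the participant will commence EEG data collection and begin keeping an electronic seizure diary". No period of study diary without EEG is described.
- **Feedback.** The same section says that "participants will receive a minimum of monthly feedback regarding recorded EEG data from their treating clinician". The abstract's Methods give the source: "The treating clinician will communicate information from this annotation report to participants monthly". Clinicians receive the summary weekly (section 3.2), and monthly feedback may use any agreed medium (section 3).
- **Content.** Table 1, objective 4, asks participants to rate a statement that begins "I found the feedback about when seizures had occurred according to the 24/7 EEG". What is passed on therefore includes the timing of seizures.
- **Primary contrast.** Table 1 pairs monthly diary counts with the research team's reading of the EEG "across the 6 months of the study (‘correlation B"). Section 4.1 frames the gain from the device as "compared to using self‐reported participant diary alone" and tests whether "the correlation between 24/7 EEG SubQ detected seizures and ground truth is higher than between the diary and ground truth".
- **Historical controls.** Section 4.2 and Table 1, objective 11, use them for patient-reported outcomes and service use, not for diary accuracy.

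**The concern.** Once told that the EEG showed seizures they had not recorded, participants can respond in several ways. They may add the missed events to the diary, watch more closely and record better, or stop bothering because the device is counting. Each changes the monthly counts that enter correlation B.

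B is subtracted from A to form the primary contrast, so any shift in B passes straight into the result. A rise in B hides part of a real advantage of the device; a fall manufactures an advantage. In either case the trial would not show how well a diary performs without EEG feedback, which is what the Introduction's case against diaries concerns and what the wording in section 4.1 implies.

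This is separate from the fact that A and the reference standard share one recording. The diary would be exposed to feedback even if the reference came from an independent source.

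**Working it through.** **1. Do the exposure and the measurement overlap?**

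| Element | Period | Where stated |
|---|---|---|
| Study diary | from Visit 3, through the 6 months | section 3; Table 1 |
| EEG recording | Visit 3 to Visit 5 | section 3.1 |
| Feedback to participant | at least monthly during the 6 months | section 3; abstract |
| Counts used for B | all 6 months | Table 1 |

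The overlap is complete apart from the stretch before each participant's first feedback. That stretch lasts at most about one month if the schedule is kept. It may be shorter, because monthly is a minimum.

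**2. Reproduce the plan's power.** Section 2.4 gives B = 0.30, SD 0.41, A = 0.5, alpha 0.05, n = 33 and power 85%. It does not state whether the test is one- or two-sided. Take 0.41 as the SD of the within-participant difference:

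- standardised difference: d = (0.5 − 0.3)/0.41 = 0.488
- noncentrality: d × √33 = 2.80, with 32 degrees of freedom
- critical t: 1.694 one-sided, 2.037 two-sided

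The paired t test has power 86.4% one-sided and 77.6% two-sided. For the Wilcoxon signed-rank test named in section 4.3, with the effective sample size set to 33 × 3/π for normal differences, power is 84.9% one-sided and 75.5% two-sided. The stated 85% is therefore matched by the one-sided Wilcoxon calculation.

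**3. Let B move, holding A = 0.5, SD 0.41 and n = 33.** The shifts in B are assumptions, since the documents give none.

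| B | A − B | d | Noncentrality | t, one-sided | t, two-sided | Wilcoxon, one-sided |
|---|---|---|---|---|---|---|
| 0.30 | 0.20 | 0.488 | 2.80 | 86% | 78% | 85% |
| 0.35 | 0.15 | 0.366 | 2.10 | 66% | 53% | 64% |
| 0.40 | 0.10 | 0.244 | 1.40 | 39% | 27% | 38% |

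**4. Let A move as well.** Section 2.4 chose 0.5 to size the study, and the true value may be higher. At B = 0.40:

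- A = 0.6: the difference is again 0.20, so power is again 86% (78% two-sided).
- A = 0.7: the difference is 0.30 and power is 99% (98% two-sided).

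In both cases the estimated difference is still 0.10 smaller than it would have been with B at 0.30.

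**5. Can the shift in B be modelled?** Only under assumed reporting behaviour. A simulation tuned to the planning values starts at B = 0.31. It reaches 0.40 if 25% of otherwise missed seizures are entered from month 2, and 0.46 if 50% are. Another, with a different reporting model, starts at 0.48 and reaches 0.65 and 0.79 when diary counts move 25% and 50% of the way to the EEG count. Both show that a shift of material size is plausible; neither estimates it for this trial.

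**The case against.** **Direction.** The more likely response to feedback may be better recording, which works against the hypothesis that A exceeds B and so is conservative for a claim of superiority. This has weight, but diary fatigue works the other way and nothing in the article rules it out. A conservative bias would also still cost power and understate the difference.

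**Diary rules not shown.** Whether past months can be edited depends on entry windows and locks that a condensed article leaves to the full protocol, so a reader should not infer that back-filling will occur. This stands. A lock, however, would not prevent learning or disengagement after feedback, and those follow from the schedule the article does state.

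**Meaning of alone.** The word may only mean that the counts come from the diary and not from the EEG, and feedback is part of the intervention. That is a fair reading of the wording. It does not change what B measures, and the sentence invites the reader to take B as ordinary diary performance.

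**Number of exposed months.** It is tempting to say that exactly five of the six monthly pairs follow feedback. The documents set only a minimum frequency, so first feedback may come before the end of month 1.

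**Size of the power loss.** The 39% requires A to be exactly 0.5. A is computed from the same recording as its reference and may well be higher, and step 4 shows power restored at A = 0.6. A reader might infer from the 39% that the trial is underpowered; the documents do not support that.

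**Conclusion.** The point holds as a mismatch between the named and the measured comparator. B describes a diary kept under at least monthly EEG feedback, over the period used for the primary contrast, and it can be contaminated by that feedback.

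A reader might go further and conclude that the contrast is biased by a known amount or in a known direction. The documents do not support that, because they give no rate of back-filling, learning or disengagement.

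The power figures are a sensitivity range. They rest on A = 0.5, on SD 0.41 as the SD of the paired difference, on n = 33 and on assumed values of B. What does not depend on those assumptions is that any shift in B moves the estimated A minus B by the same amount in the opposite direction, whether or not the test remains significant.

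**What to change.** 1. **Primary analysis.** Count for B only diary entries time-stamped before the feedback contact that covers the dates concerned. Log the date of every feedback contact, whatever medium is used.
2. **Pre-specified sensitivity analyses.** Report diary sensitivity and agreement of counts with the reference in the period before each participant's first feedback, and the trend in diary sensitivity over the 6 months. These can expose learning or disengagement, which the time-stamp rule cannot remove. The pre-feedback analysis should not be a within-participant correlation, because a single month gives only one pair of counts per participant.
3. **Wording.** In section 4.1, describe the comparator as a diary kept under monthly EEG feedback, and limit the conclusion to that.

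The feedback schedule stays unchanged. The cost is an extraction rule, a dated log of feedback contacts and the additional sensitivity analyses. The rule needs usable time stamps from the electronic diary, which the article does not describe and which should be confirmed. The downside is that some genuine late entries will not be counted.
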